### 5.1.3 Conservation

FLYP must be stored in its packaging at a temperature of between +2°C and +25°C. Under these conditions, the maximum shelf life is two years.

The product can be used between 0 and 40°C.

Reconstitution at room temperature should be completed within six minutes. The resulting solution is practically free of suspended particles.

FLYP should be used no later than 6 hours after reconstitution.

### 5.1.4 Labels

- 1 Product identification label with lot number, expiration date,
- 3 Detachable labels indicating the lot number

### 5.1.5 Reconstitution

- Remove the protective cap from both units and disinfect the surface of each cap.
- First, **pierce the stopper of the water for the injection bottle with** one of the bevels of the transfer system, then pierce the stopper of the bottle containing the lyophilized with the free bevel of the transfer system; make sure that all of the water flows onto the powder by making a rotary movement to moisten the maximum surface of the powder.
- To facilitate reconstitution, gently shake the bottle by horizontal rotations so that the water touches all the powder without making too much foam (do not shake violently).

777 - Wait for 3 to 5 minutes for complete dissolution before injecting. FLYP appears as a mostly cloudy liquid, with  
778 occasionally visible particles that are not signs of spoilage.  
779

#### 780 **5.1.6 Transfusion**

781  
782 - Check that the glass unit is undamaged before transfusion. Under no circumstances should the contents of damaged  
783 units be infused.  
784 - Transfuse intravenously immediately and in a single dose over 5 to 15 minutes per unit.  
785

#### 786 **5.1.7 Disposition of units**

787  
788 Any unused product will be returned to the CTSA.  
789 Any used product or waste will be disposed of on-site in conformity with the hospital procedure (Incineration of  
790 hospital waste - DASRI).  
791

#### 792 **5.1.8 Plasma Traceability**

793  
794 Labels to detach from the bottle and stick on:  
795  
796 - the prescription form for the delivery and the clinical and biological follow-up of the Lyophilized plasma (to  
797 be returned to the CTSA)  
798 - the medical clinical observation form (which contains the patient's source data)  
799 - the CRF of the study  
800

### 801 **5.2 PHYSIOLOGICAL SERUM**

802  
803  
804

#### 805 **5.2.1 Indications**

806 Prehospital severely injured patient, following the guidelines.  
807

#### 808 **5.2.2 Packaging and unit shape of the product**

809 Flexible bag containing 500 ml

#### 810 **5.2.3 Conservation**

811 At room temperature

#### 812 **5.2.4 Label**

813 The label is put on the top of the kit "study bag," which contains the two saline bags. It contains the  
814 following items  
815 - Name of the study  
816 - Patient number  
817 - Lot number

#### 818 **5.2.5 Administration**

819  
820 The solution is ready to use.  
821  
822

### 823 **5.3 Permitted and prohibited treatments in the protocol**

824

825 All treatments usually used to manage an acute bleeding victim are allowed and should be noted in the observation  
826 book.  
827

828 CAUTION: Do not administer clotting factors before the final blood sample for PT as this will render the observation  
829 unusable.

830 The administration of tranexamic acid is authorized and even planned on a systematic basis as soon as possible while  
831 respecting the contraindications. The dosage should be 1 gram in the prehospital setting.  
832

#### **5.4 Monitoring of the infusion/ transfusion**

For each patient, the experimental treatment, the modalities, and the chronology of administration will be collected and noted on the medical clinical observation form and the CRF.

#### **5.5 Practical procedures for accounting, storage, and delivery of experimental treatments within the investigating centers**

The experimental treatments are packaged and supplied by the CTSA. They will be distributed in batches of 2 (1 FLYP and one normal saline), either by the CTSA for the BSPP or by the regional Etablissement Français du Sang-EFS (tripartite agreement between the CTSA, the regional EFS, and the recruiting center) for the other prehospital investigating centers.

Study treatments will be stored and accounted for at each center. A copy of the detailed delivery note (date of shipment, lot number, quantity, expiry date) of the CTSA shipments will be kept there (Appendix 2). In these centers, these treatments will be stored in the in-house pharmacies under the same conditions as the other treatments routinely used in the prehospital setting but in a space specifically dedicated to the study.

Only one experimental treatment (bag containing FLYP or not) will be made available to the prehospital team in the AR or in the SMUR.

This treatment will be taken out of its packaging only when it is used.

As soon as the physician comes back from the intervention, he must return all the study elements to the center's manager.

No vial of FLYP from an opened batch shall be present in any AR/SMUR.

Unused, expired or unused FLYP units will be redirected to the CTSA.

Any FLYP that has not expired but is not usable due to improper storage conditions or any other reason must also be returned to the CTSA (with details of nonconformities) for inspection.

Suppose the FLYP is destroyed by the user (degradation without the possibility of a return to the CTSA) or in case of loss. In that case, the delivery slip will be returned to the CTSA with the mention destruction or loss of product at the level of the batch number, a duplicate will be kept at the concerned recruiting center.

Used and empty bottles will be thrown away (Incineration of hospital waste - DASRI).

### **6 EVALUATION OF THE EFFECTIVENESS OF THE TREATMENT**

#### **6.1 Description of effectiveness evaluation parameters.**

##### **6.1.1 Clinical parameters**

During the patient's care at the intervention site, vital signs (BP, HR, and consciousness) are continuously monitored from the arrival of the first aid, then the arrival of the AR or the SMUR until the arrival at the hospital.

##### **6.1.2 Biological parameters**

Improvement of biological parameters of hemostasis:

Variation between PT/INR at hospital admission and initial field PT/INR in the 2 FLYP(+) and FLYP(-) groups.

#### **6.2 Planned methods and timing for measuring, collecting, and analyzing effectiveness metrics**

Is responsible for the proper routing of blood tubes and the retrieval of results to be reported in the CRF:

- The prehospital co-investigator for the initial assessment
- The hospital co-investigator for the in-hospital assessment

The laboratory of each hospital will be asked to analyze the tubes.

Particular attention should be paid to the identification of samples and to the conservation of samples at room temperature.

Care should be taken to ensure that the time for analysis and determination of coagulation factors is less than 6 hours.

## **7 SAFETY ASSESSMENT**

### **7.1 The vigilance during the trial**

#### **7.1.1 Definitions**

✓ **Adverse event** (article R.1123-39 of the public health code)

Any adverse event that occurs in a person who is a subject of biomedical research, whether or not the event is related to the study or to the product to which the research relates.

✓ **Adverse reaction** (article R.1123-39 of the public health code)

Any adverse reaction in humans that is relevant to biomedical research and has been judged by the investigator to be possibly related to the use of the investigational product at any dose.

✓ **Adverse Receiver Effect:**

An adverse event is any occurrence in a recipient of labile blood products that is or may be related to the administration of a blood product.

✓ **Serious adverse reaction** (article R.1123-39 of the public health code and ICH guide E2B) = **adverse reaction** which :

- leads to death
- endangers the life of the person who is the subject of the research
- requires hospitalization or prolongation of hospitalization
- causes a significant or lasting disability or handicap
- results in a congenital anomaly or malformation
- or any event deemed medically serious by a health professional

✓ **Unexpected Serious Adverse Event** (article R.1123-39 of the Public Health Code) = adverse event whose nature, severity, or evolution do not correspond to the information contained in the Investigator's Brochure (IB), for an unauthorized investigational product or in the case of an authorized product, used under the conditions of the MA, the summary of product characteristics, SPC, Instructions for Use).

✓ **New security fact** (order of May 24, 2006)

New safety data that may lead to a reassessment of the benefit/risk ratio of the research, or that may be sufficient to consider changes in the research documentation, the conduct of the research, and, if appropriate, in the use of the product

### **7.2 Investigator's responsibilities**

#### **7.2.1 Notification of AE to the sponsor**

The investigator should report all biological and clinical AEs in the CRF. and report them to the sponsor if necessary.

#### **7.2.2 What should be declared?**

• **Expected SAEs:**

○ **subject to immediate notification by the investigator:**

- Allergic reactions
- TACO (transfusion-associated circulatory overload)

In sporadic cases, transfusion of fresh frozen plasma may result in allergic reactions or respiratory complications. Therefore, it is important to observe whether the same clinical events occur with FLYP even though the method of manufacturing freeze-dried plasma reduces this risk.

- **not requiring immediate notification by the investigator**

Serious adverse events related to the natural and usual course of the disease and not related to the investigational treatment, nor the acts and procedures added by the research:

- Aggravation of hemorrhagic shock
- Any complications secondary to hemorrhagic shock
- Hospitalization for any length of time: patients suffering from hemorrhagic shock in a traumatic context will benefit from multidisciplinary care in the hospital, including intensive care, surgery, medicine, and functional rehabilitation.
- Death: as the death rate for severe trauma patients is around 50%; given the high activity of the receiving departments, the coordinating investigator must be notified of death via [name] within 72 hours. The coordinating investigator will transmit the information to the promoter (Research and Innovation [REDACTED])

- **Unexpected SAEs:**

Upon **arrival at the hospital**, the patient will be taken care of by the hospital's emergency or intensive care unit, and a follow-up of the initial workup will be performed.

- After the extension workup, a prognosis can be given. Any unexpected worsening of the patient's existing condition that is not consistent with the prognosis given by the initial extension workup should be considered an SAE and reported by the hospital investigating physician.

- **The occurrence of in utero exposure**

Any pregnancy in which the fetus (from pre-embryonic stage to birth) may have been exposed at any time to FLYP, even if not associated with an adverse event, should be reported to the sponsor without delay.

### **7.2.3 When to report?**

Immediately and no later than 24 hours after the investigator becomes aware of an SAE.

The investigator ensures that relevant information regarding the follow-up is communicated to the sponsor within seven days.

Any SAE must be reported, if it occurs for a research participant, during the entire duration of the research, i.e., from the date of signature of the consent form until the end of the participant's follow-up, i.e., 30 days after inclusion in the protocol, or at the patient's death if this occurs during the follow-up period.

Once the trial is completed, the investigator is not required to actively follow participants for adverse events. After the end of follow-up, serious adverse events experienced by a participant will still be reported to the sponsor if the investigator is aware of them.

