### **4.7 Procedures for obtaining consent from research subjects**

All selected patients who meet the inclusion criteria will be offered to participate in the study. They will be informed orally about the study and the different examinations performed by the prehospital or hospital investigating physician.

Consent must be obtained primarily from the person who is to be the subject of the research.

However, in view of article L. 1122-1-2 of the Public Health Code, if the urgency of the situation does not allow the consent of this person, it is requested from the family or the trusted person if they are present.

If consent could not be obtained prior to administration of the experimental treatment, the patient may be included by decision of the investigator, and consent will be sought from the patient as soon as his or her condition permits for the continuation of the research.

In the event that the patient dies after emergency inclusion, but before he or she is able to sign the consent to proceed, the data will be retained for the research. If possible, the investigator will inform the family.

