### **7.4 Planned methods and timing for measuring, collecting, and analyzing safety assessment metrics**

#### **During the prehospital phase:**

A permanent presence of an emergency physician and a nurse with the person undergoing research. Continuous surveillance of the clinic, continuous monitoring of the constants: HR, BP, SpO2. Verification of the absence of signs of drug intolerance.

Collection of the different parameters in the prehospital CF.

The occurrence of adverse event(s) or the aggravation of adverse event(s) in the prehospital phase will be reported by the physician who managed the patient in the context of prehospital management.

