## 7.5 Data Safety Monitoring Board (DSMB/ CSI)

An oversight committee made up of members independent of the project will be set up:

Department of anesthesia and intensive care

Hematology-Transfusion Unit

This committee is informed during the study of any AE/SAE related to the administration of FLYP.

He is informed, in writing, by the promoter, and the information relating to the follow-up of the AEs will be transmitted to him.

It will be responsible for ruling on the causality of AEs reported by investigators during the trial. It has an advisory function when called upon by the sponsor on medical issues such as tolerance and adverse events.

The committee will decide whether or not to stop the study and whether or not to discharge the patient from the study. The recommendations concerning the continuation, possible modifications, or premature termination of the study will be transmitted to the sponsor.

This committee meets once every six months, except in particular cases.

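### The SAE reporting window opens at consent signature although treatment may precede consent, and no stated process gives the DSMB deaths or SAEs by arm during the trial

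*Combined protocol and SAP*

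**What the plan says.** **Reporting window.** Protocol section 7.2.3 states "Any SAE must be reported, if it occurs for a research participant, during the entire duration of the research". The same sentence then defines that period as running "from the date of signature of the consent form until the end of the" participant's follow-up, which it places at 30 days after inclusion, or at death if sooner. The deadline is 24 hours after the investigator learns of the event.

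**Consent.** Section 4.7 states "If consent could not be obtained prior to administration of the experimental treatment, the patient may be included by decision of the investigator", with consent to continue sought once the patient's condition allows. If the patient dies "before he or she is able to sign the consent to proceed, the data will be retained for the research".

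**Prehospital events.** Section 7.4 states "The occurrence of adverse event(s) or the aggravation of adverse event(s) in the prehospital phase will be reported by the physician" who treated the patient. It sets no consent condition.

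**Deaths.** Section 7.2.2 lists worsening shock, its complications and death among the expected serious events that belong to the course of the injury and need no immediate notification. On death it reads "Death: as the death rate for severe trauma patients is around 50" per cent. The coordinating investigator is to be told within 72 hours and then informs the sponsor.

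**DSMB.** Section 7.5 states "This committee is informed during the study of any AE/SAE related to the administration of FLYP". The committee also adjudicates the cause of events that investigators report, decides whether the trial should stop, and meets every six months. Section 8.4 rules out an interim analysis.

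**The concern.** There are two separate weaknesses.

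First, the section that tells investigators when the SAE duty applies ties its start to an act that, in an emergency trial, may come after treatment or not at all. An investigator who follows 7.2.3 to the letter and one who follows 7.4 would handle the same prehospital event differently. Ascertainment could then differ between centres, in the period when reactions to the infusion are most likely to show. Section 9.1 makes this harder to check: without a signed form, the sponsor's monitors have no direct access to the medical data and depend on the local principal investigator's answers.

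Second, the committee that decides on stopping is told of events related to the plasma. When death is common and expected, harm appears as an imbalance between the arms and not as one attributable case. Reviewing causality case by case cannot show such an imbalance; a table by arm can.

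**Working it through.** The plan contains no calculation for safety monitoring, so there is no figure to reproduce. The check sets the sections side by side and then sizes the second limb from the plan's own inputs.

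**1. The window in section 7.2.3, read literally, for the patients section 4.7 allows**

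| Patient | Signature | Window | Transfusion inside it? |
|---|---|---|---|
| Patient or relative signs before treatment | before | signature to 30 days after inclusion | yes |
| Emergency inclusion, signed later | after | signature to 30 days after inclusion | no |
| Emergency inclusion, dies with no signature | never | does not open | no |

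The second and third rows conflict with section 7.4. The sentence is also inconsistent in itself, because it starts from signature and ends by counting from inclusion. The SAP (Timing of outcome assessments) uses inclusion as time zero throughout. The broader phrase about the whole duration of the research does not settle the matter, because the sentence goes on to define that duration by the signature.

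**2. Provisions that capture events at transfusion without a consent condition**

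- Section 3.3.5: adverse events are marked in the prehospital column of the schedule.
- Section 3.9: reactions to administration are source data in the case report form.
- Section 4.4: an adverse event on study treatment leads to a meeting of the independent committee.
- Section 7.2.1: all adverse events go in the case report form.
- Section 7.2.2: allergic reactions and circulatory overload need immediate notification.
- Section 7.2.4: haemovigilance events are declared without delay.
- Section 7.4: the prehospital physician reports.

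**3. Deadlines**

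Section 7.2.3 sets 24 hours for an SAE and names no exception. Section 7.2.2 exempts some serious events from immediate notification and sets 72 hours for death. The second may be meant as an exception to the first, but the text does not say so.

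**4. What reaches the DSMB**

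The stated flow is plasma-related events (7.5) and the ad hoc meeting in 4.4. The stated route for deaths is investigator, coordinating investigator, sponsor (7.2.2), with no onward step to the DSMB. Sections 3.6 and 3.7 tie early stopping to unexpected serious events, unanticipated events or new product information. Survival and adverse events by arm appear in the final analysis (protocol 8.1; SAP, Timing of final analysis and Harms).

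**5. Size**

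Inputs: 140 patients, 70 per group (Summary); mortality about 50% (7.2.2); inclusion over 30 months (Summary); a meeting every 6 months (7.5). Even accrual is an assumption.

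- Deaths in total: 140 × 0.50 = 70.
- Meeting intervals: 30 / 6 = 5.
- Patients per interval: 140 / 5 = 28.
- Deaths per interval: 28 × 0.50 = 14.
- Sensitivity: with 40% mortality, which sections 1.2 and 1.3 attach to patients with coagulopathy, 140 × 0.40 = 56 deaths and 56 / 5 = 11.2 per interval.

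For scale, assume 50% mortality under standard care and 60%, 65% or 70% with plasma. The excess among 70 plasma patients is 70 × 0.10 = 7, 70 × 0.15 = 10.5 or 70 × 0.20 = 14 deaths. A two-sided 5% comparison of two proportions, standing in for the planned log-rank test, has power Φ{[d − 1.96·√(2·p̄(1−p̄)/70)] / √[(p₁(1−p₁)+p₂(1−p₂))/70]}, where d = p₂ − p₁ and p̄ is the mean of p₁ and p₂. This gives 22%, 43% and 68%. At d = 0.10: (0.10 − 1.96 × 0.0841) / 0.0837 = −0.77, and Φ(−0.77) ≈ 0.22.

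**The case against.** The strongest reply is that one phrase in 7.2.3 is being set against a whole safety system. Much of that reply stands, and it rules out several stronger readings that a reader might infer.

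- **That harms at transfusion go unreported or unreviewed.** The documents do not support this. The seven provisions in step 2 apply whatever the consent status, section 4.4 brings in the committee, and the safety population is all randomised patients (8.7; SAP, Analysis populations). What is shown is a contradictory rule.
- **That most patients are affected.** The documents give no share of deferred consent. Section 4.7 seeks the patient's consent first, then that of a relative or trusted person if present.
- **That the DSMB sees nothing but plasma-related events.** Section 7.5 does not contain the word only. A committee that adjudicates causality presumably sees some events before they are classed as related. The section is ambiguous on this. Even on the generous reading, it provides for rulings on single cases and not for counts by arm.
- **That nobody can compare deaths by arm before the end.** The sponsor could. The trial is open-label (3.8), the SAE form states the treatment (7.2.4), the sponsor's service holds the randomisation list jointly (3.2.2), and the sponsor writes a yearly safety report (7.3). But that report lists potentially product-related SAEs with an unspecified safety analysis, and goes to the authority and the ethics committee. Nothing requires a by-arm mortality count or sends one to the DSMB.
- **That every death is classed as unrelated.** Section 7.2.2 also makes worsening that does not fit the prognosis a reportable unexpected SAE.

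Finally, all 70 deaths exist only at full enrolment, when survival is compared anyway. The relevant quantity is therefore the number per meeting, and any particular split of deaths between the arms would be illustrative.

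**Conclusion.** The point holds on both limbs and should be fixed.

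On the window, 7.2.3 is wrong as written for any patient treated before a signature. It conflicts with 4.7, with 7.4 and with its own end point. The likely consequence is uneven application between sites, since capture is provided for elsewhere. The number of patients concerned cannot be given from the documents.

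On the DSMB, no stated process gives it deaths or SAEs by arm during the trial. About 14 deaths would fall between consecutive meetings, assuming 50% mortality and even accrual over 30 months (about 11 at 40%). Slower accrual lowers the number per meeting but not the total. The assumed excesses of 7 to 14 plasma-arm deaths show that an imbalance could build up without any document requiring that the committee see it. They are not a prediction.

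**What to change.** 1. In protocol section 7.2.3, replace the date of consent signature as the start of the window with: *inclusion (randomisation), whether or not consent has yet been signed*. This matches the sentence's end point, section 7.4 and the SAP's time zero.
2. Reconcile the 24-hour rule in 7.2.3 with the 72-hour and non-immediate rules in 7.2.2, stating which events are exceptions.
3. In section 7.5, state that each six-monthly meeting receives a closed table of all deaths and all SAEs by arm, whatever the investigator's view of causality, with no efficacy test.

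The cost is a few sentences and one extra closed table per meeting, about five over a 30-month inclusion period. Because no efficacy endpoint is tested, there is no alpha to spend and section 8.4 can stand. Patient care does not change.
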